#### Statistical analysis

Analyses will be conducted using Stata (StataCorp, College Station, TX, USA) and will follow the intention-to-treat principle.

Feasibility outcomes, including recruitment, retention, intervention adherence, and data completeness, will be summarized using descriptive statistics with corresponding 95% confidence intervals.

Continuous outcomes will be analyzed using linear mixed-effects models, including fixed effects for group, time, and group-by-time interaction, and random effects to account for within-subject correlation over time. Where appropriate, model assumptions will be assessed and alternative analytical approaches considered if necessary.

Results will be presented as estimated effect sizes with 95% confidence intervals. Given the feasibility nature of the study, no formal hypothesis testing is planned, and *p *values will be interpreted with caution.

Given the study design, analyses of secondary outcomes are exploratory and are not intended to evaluate intervention effectiveness. Instead, they are intended to estimate outcome variability and to inform the design, outcome selection, and sample size calculation of a future definitive randomized controlled trial. The extent, pattern, and completeness of outcome data will be described for each outcome and follow-up assessment and will be considered when interpreting the feasibility of the study procedures.

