### Randomization and blinding

Randomization is performed after completion of baseline assessments using a computer-generated randomization sequence with block randomization, stratified by ward security level (security classes I–III). Stratification by ward security level was chosen because patients treated in different security levels may differ regarding psychiatric severity, level of supervision, access to rehabilitation activities, and opportunities to engage in lifestyle-related interventions, all of which may influence the feasibility and delivery of the intervention. Participants are not matched, as randomization is considered sufficient to ensure group comparability in this feasibility trial. An independent digital randomization table is generated using a secure web-based randomization service (www.sealedenvelope.com) to ensure allocation concealment prior to assignment.

The randomization sequence is generated in advance and implemented by a member of the research team not involved in recruitment or baseline assessment. Due to the nature of the intervention, the study is open label. Where feasible, data analysis will be conducted without knowledge of group allocation.

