### Assessments

Assessments are conducted at baseline, 6-month follow-up, and 12-month follow-up and include:Anthropometric measurements (body weight, height, BMI, waist-to-hip ratio) [35–37]Blood pressure measurementBlood sampling (fasting plasma glucose, HbA1c, lipid profile)A structured lifestyle questionnaire covering physical activity, diet, tobacco use, and alcohol consumptionHealth-related quality of life assessed using EQ-5D-5L [38–40]Mental fatigue assessed using the Mental Fatigue Scale (MFS) [41, 42]

These assessments are performed independently of the intervention sessions and are used to evaluate changes in cardiometabolic risk and lifestyle factors over time.

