### Sample size and statistical analysis

#### Sample size rationale

This study is designed as a randomized controlled feasibility trial with primary objectives focused on recruitment, retention, acceptability, intervention delivery, and completeness of data collection in compulsory forensic psychiatric care and a secondary, explorative evaluation of intervention impact on clinical outcomes. A total of 50 participants (25 per group) will be recruited.

A formal sample size calculation was undertaken based on a clinically meaningful change in the health curve, in order to evaluate a potential impact of the intervention on clinical outcomes related to the secondary, exploratory aim. Consistent with prior evaluations of the SHD model, a clinically relevant response was defined as a priori as an improvement of at least one risk category between baseline and follow-up. The proportion of participants achieving such an improvement was conservatively assumed to be 0% in the control group and 30% in the intervention group. Using a two-sided significance level of 5% (*α* = 0.05) and a power of 90% (1 − *β* = 0.90), this corresponds to a required sample size of 25 participants per group.

Although this calculation indicates that the planned sample allows preliminary exploration of change in this outcome, the study is not intended to provide conclusive evidence of effectiveness. Analyses of clinical outcomes will therefore be interpreted as exploratory and used to inform the design of a future definitive randomized controlled trial.

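### The mixed model for continuous outcomes gives each arm its own baseline mean although baseline precedes randomisation, which costs precision in the exploratory treatment contrasts

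*Protocol article*

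**What the plan says.** The Statistical analysis section of the protocol article describes the models for continuous outcomes as "including fixed effects for group, time, and group-by-time interaction, and random effects to account for within-subject correlation over time". It names no baseline covariate, no shared baseline mean and no stratification factor.

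The Assessments section sets the levels of time: "Assessments are conducted at baseline, 6-month follow-up, and 12-month follow-up". The Randomization and blinding section sets the order of events: "Randomization is performed after completion of baseline assessments". It also describes "block randomization, stratified by ward security level", on the ground that "patients treated in different security levels may differ regarding psychiatric severity, level of supervision, access to rehabilitation activities". The Sample size rationale gives the numbers: "A total of 50 participants (25 per group) will be recruited".

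The Statistical analysis section adds that results will be reported as effect sizes with 95% confidence intervals, that no formal tests are planned, and that the secondary analyses serve to plan a later definitive trial.

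**The concern.** With baseline as a level of time, the group main effect is the difference between arms at baseline. Because randomisation comes afterwards, that difference is known to be zero in expectation. Estimating it freely spends information on a known quantity, and the group-by-time term at 12 months becomes the difference between arms in mean change from baseline. A model that holds the baseline means equal, or that conditions on baseline, uses the same data and gives a tighter interval.

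What is at stake is the width of the confidence intervals for the secondary continuous outcomes, such as blood pressure, HbA1c, lipids, EQ-5D-5L and the Mental Fatigue Scale. As no formal tests are planned, the estimates and their intervals are the main product of these models.

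**Working it through.** **Inputs from the protocol article.** n = 25 per arm (Sample size rationale); three visits at baseline, 6 and 12 months (Assessments); baseline before randomisation (Randomization and blinding); fixed effects for group, time and their interaction (Statistical analysis). The article gives no precision figure for the continuous outcomes. Its one sample-size calculation, for a binary health-curve response of 0% against 30%, reproduces with the unpooled formula: (1.960 + 1.282)² × (0.3 × 0.7)/0.3² = 24.5, rounded up to 25. This point does not depend on it.

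**Assumptions.** Outcome SD of 1 at every visit, the same correlation rho between any two visits (as a random intercept implies), and complete data. The article gives no rho, so a range is shown.

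**Stated model.** The 12-month contrast is a difference in mean change. Change has variance 2(1 − rho) per person, so the contrast has variance 4(1 − rho)/n.

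**Common baseline mean.** The contrast is that of the 12-month value given baseline, with variance 2(1 − rho²)/n.

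**Ratio.** 2(1 − rho²) / [4(1 − rho)] = (1 + rho)/2. A generalised least squares calculation over all three visits gives the same values.

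| rho | variance, stated | variance, common baseline | ratio | SE, stated | SE, common baseline | excess SE, stated |
|---|---|---|---|---|---|---|
| 0.3 | 0.1120 | 0.0728 | 0.65 | 0.335 | 0.270 | 24% |
| 0.5 | 0.0800 | 0.0600 | 0.75 | 0.283 | 0.245 | 15% |
| 0.7 | 0.0480 | 0.0408 | 0.85 | 0.219 | 0.202 | 8% |
| 0.8 | 0.0320 | 0.0288 | 0.90 | 0.179 | 0.170 | 5% |
| 0.9 | 0.0160 | 0.0152 | 0.95 | 0.126 | 0.123 | 3% |

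In participants, 25 per arm would inform like 25/0.75 = 33 at rho 0.5, 25/0.90 = 28 at 0.8 and 25/0.95 = 26 at 0.9.

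**Where the loss comes from.** A chance baseline difference has SE √(2/25) = 0.283 SD. Given an observed difference d, the change contrast is displaced by (1 − rho)d in magnitude. Averaged over randomisations this adds no bias but adds variance (1 − rho)² × 2/n: 0.02 at rho 0.5 (0.08 − 0.06) and 0.0032 at rho 0.8 (0.0320 − 0.0288). This is the whole of the loss, not a second defect.

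**Missing data.** With 20% missing at 12 months, the ratio of the SEs (common baseline to stated) moves from 0.866 to 0.886 at rho 0.5 and from 0.949 to 0.957 at rho 0.8. Most of the gain remains.

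**Other reading of time.** If time meant only 6 and 12 months, baseline would go unused. The 12-month contrast would have SE 0.283 whatever rho is, against 0.245 at rho 0.5 and 0.170 at rho 0.8 when baseline is used. Precision is lost on either reading.

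**Security level.** Let it explain a share R² of total variance (assumed 5–20%) as a subject-level main effect.

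- Added to the stated model, the variance of change is 2[(1 − R²) − (rho − R²)] = 2(1 − rho). Nothing changes.
- Added to the common-baseline model, the conditional variance is (1 − R²) − (rho − R²)²/(1 − R²). At rho 0.5 this is 0.737 (R² 0.05) or 0.688 (R² 0.20) against 0.75, so the SE is 0.9% or 4.3% lower. At rho 0.8 it is 0.358 or 0.350 against 0.36, so the SE is 0.3% or 1.4% lower.

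**The case against.** The strongest reply is that this is a loss of efficiency, not bias, in analyses that the article itself calls exploratory. The primary feasibility outcomes are summarised descriptively and the health-curve response is binary, so neither is touched. If the outcomes track strongly over time, the penalty is a few per cent. All of that stands and limits the weight of the point. It does not remove it: a model is stated, one of its listed terms causes the loss, and intervals are what will be reported. The section's allowance for other methods is tied to checks of model assumptions and does not commit the analysis to using baseline.

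A reader might infer four stronger things, which the documents do not support.

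- *Leaving out security level makes the intervals some 3–12% too wide.* That comes from 1/√(1 − R²) with R² of 5–20%, but a subject-level main effect cancels from the stated change contrast, as shown above. The article also does not say that its list of terms is complete; covariates may be left to an analysis plan that is not shown.
- *The variability passed to the definitive trial must be that of change scores.* A mixed model with subject random effects yields between-subject and residual variance separately, so the baseline-adjusted variance can be derived from the stated fit.
- *Chance imbalance biases the result.* Over repeated randomisations it does not.
- *The remark "Participants are not matched, as randomization is considered sufficient to ensure group comparability in this feasibility trial" is an analytic error.* It explains why participants are not matched and does not settle the model.

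**Conclusion.** The point holds for baseline. Read together, the Assessments, Randomization and blinding, and Statistical analysis sections describe a model that estimates a baseline difference known to be zero, so the group-by-time contrast is less precise than the collected data allow. The standard error is about 15% larger than necessary at rho 0.5, 5% at 0.8 and 3% at 0.9. These figures rest on an assumed rho, equal correlation between visits and complete data. The loss is one of precision only, confined to the secondary exploratory continuous outcomes. The missing security-level term is not a fault in itself; it belongs in the remedy, where it brings a small additional gain. The change is worth making because it is nearly free, not because the stated analysis would mislead.

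**What to change.** In the Statistical analysis section, replace the description of the fixed effects with wording such as: *Time is treated as categorical (baseline, 6 and 12 months). Baseline means are constrained to be equal across arms, with no group effect at baseline, and group effects are estimated at 6 and 12 months. Ward security level, the stratification factor, is included as a fixed main effect.*

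No stratum-by-time interaction is needed. Regressing the 6- and 12-month values on baseline also recovers the precision, but it is not the same model: it drops anyone without a follow-up value. One of the two should be named.

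The cost is one sentence and two degrees of freedom for the three security levels, against one baseline parameter saved. No new data are needed, and baseline should be complete because it precedes randomisation. The change should be fixed before outcomes are examined by arm, so that the choice of model is not made after the fact.

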### Patient and public involvement

The study is informed by extensive clinical experience in forensic psychiatric care, which has guided the adaptation of the intervention and study procedures to the specific organizational and clinical conditions of compulsory forensic psychiatric inpatient care.

Patient and public involvement has been incorporated during the study planning phase and will be continuously applied through collaboration ReLife Centre at Lund University.

Findings from the study will be fed back to clinical services and are intended to support the development and implementation of sustainable preventive health interventions within forensic psychiatric settings.

### Ethics and dissemination

The study has been approved by the Swedish Ethical Review Authority. Particular attention is paid to voluntariness, autonomy, and protection of participant integrity in the compulsory care context. Results will be disseminated through peer-reviewed publications, conference presentations, and feedback on participating in clinical services.

## Trial status

Recruitment is planned to begin in February 2026 and will be conducted on a rolling basis within the participating forensic psychiatric inpatient clinic, with completion expected by December 2027. Follow-up assessments are conducted 6 and 12 months after baseline. Outcome data are expected to be collected by December 2028, with data analysis completed by the end of 2029.

## Data Availability

No datasets were generated or analysed during the current study.
